### Outcomes

2.7

The main study outcome is the IDS (30-item self-report) total score during 12-week follow-up (Rush et al., 1986, 1996, 2006, 2011). Secondary study outcomes include response (50% reduction in IDS scores), remission (MINI-S diagnostic interview) (Hergueta and Weiler, 2017), adverse side effects for antidepressants (Uher et al., 2009) and for the study medication (as used in the PREDDICT trial (Baune et al., 2021; Fourrier et al., 2018)), symptom profiles (IDS atypical, energy-related symptoms (Lamers et al., 2013);), fatigue (Vercoulen et al., 1994; Beurskens et al., 2000), food craving (Nijs et al., 2007), sleep (Johns, 1991, 1992), anxiety symptoms (Spitzer et al., 2006), functioning (Saltychev et al., 2021), pain (Hawker et al., 2011), and therapy compliance. Additionally, participants have the option to collect a stool sample at baseline and 12 week follow up for microbiome analysis, as well as allow for collection of one additional blood tube for DNA analysis. Baseline measurements will include questionnaires about life events (Brugha and Cragg, 1990), smoking, alcohol use, and physical activity (Craig et al., 2003). A full overview study measures and respective time point can be found in Table 2.

**Table 2 tbl2:**
[figure not shown]
Study measures.

### Sample size

2.8

In order to properly calibrate the sample size calculation for this longitudinal treatment study we estimated an expected effect size from similar anti-inflammatory add-on published trials. A previous meta-analysis (Köhler‐Forsberg et al., 2019) including 4 RCTs showed a significant effect of celecoxib add-on, as compared to placebo, to standard first line (SSRI/SNRI) antidepressant treatment with a pooled standardized mean difference (SMD) of −0.82 [95%CI: −1.17, −0.46]. We calculated a standardized effect size from the recent PREDDICT trial (Baune et al., 2021) showing no significant difference between placebo versus celecoxib add-on to vortioxetine. From this trial, the differences in means in the two treatment groups at the end of the treatment were standardized using baseline standard deviations, obtaining a SMD of 0.30 [95%CI: −0.06, 0.66]. We pooled the effect sizes for all the 5 trials mentioned above using a random effect meta-analysis (see forest plot below). The pooled SMD was −0.52 [95%CI: −1.05, 0.01] which we used in subsequent power calculations.

Power calculations were performed with the “powerlmm” package (Power Calculations for Longitudinal Multilevel Models, v. 0.4.0) in R v4.0.0 (R Project for Statistical Computing), which is based on the analytical model described in Galbraith and Marschner (2002). We considered a study design with 6 follow-up repeated assessments of depressive symptoms with an ICC of 0.5 and an overall SMD of −0.52 (see Fig. 2) between treatment groups (1:1 ratio) across the follow-ups. We additionally modelled attrition based on the recent results of the PREDDICT trial (Baune et al., 2021), reporting drop-outs of 16% in the placebo add-on group and 12% in the celecoxib add-on at the end of the treatment. Under these assumptions, a sample size of 140 subjects allows to detect a significant (α = 0.05) treatment-by-time interaction effect with 83% statistical power.

**Fig. 2 fig2:**
[figure not shown]
Standardized Mean Difference of previous RCTs.

### Randomization

2.9

Double-blind randomization is performed using block randomization in Castor EDC (ratio 1:1, celecoxib n = 70, placebo n = 70). The randomization codes are kept by the hospital pharmacy, no involved researchers have access to the randomization list. Both capsules and bottles of the placebo and study medication are identical in appearance. For safety reasons participants can be deblinded by a designated staff member, not involved with the study, if deemed necessary.

### Data analysis

2.10

Analyses will be performed following an Intention-To-Treat principle: all participants will be included in the analysis according to their allocated treatment group at randomization. The primary outcome will be analysed using data from all post-randomization time points: 2-week, 4-week, 6-week, 8-week, 10-week and 12-week assessments. Given the correlation between repeated measures within subjects, linear mixed models will be used including a random intercept at subject level. Linear mixed models are able to handle missing data using maximum likelihood estimation. In the primary analysis, fixed effects will consist of treatment, a linear effect of time, and a treatment-by-time interaction. In secondary analyses, time will be dummy-coded and all two-way interactions between treatment and time dummies will be entered in the model to allow the estimation of group means at each time point. Estimates will be adjusted for the baseline IDS scores. Standardized effect sizes will be computed by dividing the estimated mean treatment group difference (across the overall follow-up and at each follow-up assessment) by the SD of the baseline outcome. The statistical significance threshold will be set at α = 0.05, two-sided. Analysis for the secondary outcomes will follow the same approach as the primary outcomes. Descriptive statistics will be calculated for adverse events. All statistical analyses will be performed using R or SPSS.

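### With a random intercept as the only named subject-level effect, the powered treatment-by-time test exceeds its 5% error rate if patients' slopes differ or correlation decays between visits

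*Protocol article*

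**What the plan says.** Protocol article, section 2.10 (Data analysis): because repeated measures within a subject are correlated, "linear mixed models will be used including a random intercept at subject level". In the primary analysis, "fixed effects will consist of treatment, a linear effect of time, and a treatment-by-time interaction". The data are the "2-week, 4-week, 6-week, 8-week, 10-week and 12-week assessments". On covariates and error rate: "Estimates will be adjusted for the baseline IDS scores" and "The statistical significance threshold will be set at α = 0.05, two-sided". A secondary model replaces linear time by visit dummies, and the secondary outcomes are to be analysed in the same way. No random slope, serial correlation, unstructured covariance or robust standard error is named.

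Section 2.8 (Sample size) assumes "6 follow-up repeated assessments of depressive symptoms with an ICC of 0.5" and "an overall SMD of −0.52", with dropout of 16% (placebo) and 12% (celecoxib). It reports 83% power for the treatment-by-time interaction with 140 subjects. The ICC is the only variance parameter given.

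**The concern.** A random intercept as the sole source of within-patient correlation makes weeks 2 and 4 correlate exactly as weeks 2 and 12 do, and makes the variance the same at every visit. Biweekly symptom scores need not behave so. The article itself calls depression heterogeneous (section 1), asks for whom celecoxib works (section 1.2), and lets patients start psychotherapy during the trial (section 2.4.1). All of this makes unequal rates of change plausible.

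When slopes differ, the model puts that variation into the residual and treats it as independent from visit to visit. The slope contrast is where this does harm, and the interaction is the effect on which the sample size rests. At stake is whether a significant interaction carries the 5% false-positive rate that the plan states.

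**Working it through.** **Inputs.** From the article: 70 per arm, six visits (m = 6), ICC 0.5, SMD 0.52, dropout 16%/12%, two-sided alpha 0.05. Set the baseline variance to 1, so the intercept variance is 0.5 and the residual variance s2e is 0.5. Measure time in units of 12 weeks (1/6, 2/6, ..., 1), which gives a sum of squares about the mean of SSt = 0.486. Assumed, because the article does not give it: the between-patient slope SD, tau, in baseline SDs per 12 weeks.

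**The plan's own figure.** With tau = 0 and no dropout, SE(interaction) = sqrt(2 × 0.5 / (70 × 0.486)) = 0.171. For a slope difference of 0.52 per 12 weeks, power = Phi(0.52/0.171 − 1.96) = 85.8%. With dropout rising linearly to 16%/12%, the SE is 0.181 and power is 82.1%, close to the stated 83%. This reproduction is not unique. If the full 0.52 accrues between the first and last of 6 or 7 assessments, power with dropout is 93.2% or 95.3%. Under those codings 83% would need tau of about 0.54 or 0.60.

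**Type I error with unequal slopes.** The true variance of the interaction estimate is proportional to s2e + tau² × SSt. The random-intercept model credits only s2e + tau² × SSt/(m − 1). With R the ratio of the two, type I error = 2 × [1 − Phi(1.96/sqrt(R))].

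Example, tau = 0.6: R = (0.5 + 0.36 × 0.486)/(0.5 + 0.36 × 0.486/5) = 0.675/0.535 = 1.262. Then sqrt(R) = 1.123, and the type I error is 8.1%.

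| Slope SD | R | Type I error, analytic | Simulated |
|---|---|---|---|
| 0 | 1.000 | 5.0% | 5.0% |
| 0.2 | 1.031 | 5.4% | 5.4% |
| 0.3 | 1.069 | 5.8% | 5.3% |
| 0.4 | 1.121 | 6.4% | 6.3% |
| 0.5 | 1.185 | 7.2% | 7.4% |
| 0.6 | 1.262 | 8.1% | 8.0% |
| 0.8 | 1.443 | 10.3% | 10.7% |
| 0.95 | 1.597 | 12.1% | – |
| 1.0 | 1.651 | 12.7% | 13.1% |

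The simulation used 4,000 trials per row and fitted the random-intercept model by REML with the baseline covariate and the stated dropout. Neither the baseline adjustment nor likelihood handling of missing data removes the inflation.

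**Type I error with decaying correlation and constant variance.** The model's within-patient variance is 1 minus the average correlation. The true one is c'Vc × SSt, where V is the correlation matrix and c holds the least-squares slope weights.
- Linear decay from 0.60 (adjacent) to 0.45 (first to last), average 0.55: R = 0.640/0.450 = 1.42, type I error 10.0%.
- Random intercept plus AR(1) residuals with correlation 0.2 to 0.6: 8.6% to 17.9%.
- Pure AR(1), adjacent correlation 0.7, average 0.476: R = 1.244/0.524 = 2.37, type I error 20.3%.

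**Other contrasts.** With the stated dropout (1,500 simulated trials per setting, no baseline covariate), the difference averaged over follow-up rejected in 5.5% (tau = 0.6), 6.1% (tau = 0.95) and 5.5% (AR(1) 0.7). The interaction rejected in 8.5%, 10.9% and 21.3%. Visit-specific contrasts hold 5.0% under constant-variance serial correlation. With tau = 0.6 and slopes diverging from the first visit, they run from 4.1% at the first visit to 6.7% at the last.

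**Power with a valid standard error**, in the set-up that gives 82.1%: 80.6% (tau 0.2), 76.2% (0.4), 73.2% (0.5), 69.6% (0.6), 53.6% (1.0).

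**The case against.** Four objections deserve weight.

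- **The wording is not exclusive.** Section 2.10 says that the model includes a random intercept. It excludes nothing, and covariance details are often left to an analysis plan that is not shown. A reader might infer that random slopes are ruled out, and the text does not say so. Yet the article does choose a subject-level structure and names one effect, so this is a stated choice open to comment. A fallback order for non-convergence, by contrast, is analysis-plan detail and is no finding here.
- **The interaction is not designated as the sole primary test.** The main hypothesis (section 1) concerns severity over 12 weeks, and section 2.10 standardises a mean difference across follow-up. For that difference the random-intercept standard error is correct with complete data and nearly so with dropout. A reader might infer that the whole primary analysis is anti-conservative, but the defect is largely confined to the interaction. It still matters, because section 2.8 powers exactly that term.
- **The size is not in the document.** A reader might infer a false-positive rate of 8 to 20%. The article gives no slope variance or serial correlation, so the range starts at 5%. The slope SDs behind 8% and 12% (0.6 and 0.95) exceed the assumed treatment effect of 0.52, and the 20% case has no persistent patient level at all.
- **Loss of power is not established.** A reader might infer that true power is 70%. That assumes the 83% was computed with zero slope variance, and other codings reach 83% with tau of about 0.54 to 0.60. At those values, however, the random-intercept test would itself run at roughly 7.5 to 8%.

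**Conclusion.** The concern holds conditionally. As described, the test of the powered interaction keeps its 5% level only if patients' slopes are equal and correlation does not decay with time between visits, and nothing in the article supports either condition. The direction of the error under these departures follows from the algebra. Its size rests on quantities that the article does not give: negligible to small for slope SD up to 0.3, clear from about 0.5, about 10% under mild correlation decay, and up to about 20% in the extreme serial-correlation case examined. No single inflated error rate can be attributed to this trial. The averaged treatment difference is largely safe. Visit-specific contrasts are affected only mildly, and only when variance changes over time.

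**What to change.** Keep the linear-time primary model and add a subject-level random slope for time beside the random intercept. An unstructured residual covariance over the six visits, or a robust standard error, for the same one-degree-of-freedom interaction would also serve. Replacing the model by one with categorical time is not needed: that changes the test instead of repairing it, and the plan already has such a model as secondary. Allow an unstructured covariance in that secondary time-dummy model, and carry the same choices to the continuous secondary outcomes.

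Restate the 83% power with the slope variance written out and with the coding that turns the overall SMD into a slope.

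The cost is a change of text and a few lines of code, with no new data or visits. The real downside is that the valid standard error may be larger and the stated power lower, as the last line of the working shows. The change should be made before unblinding, since a later change of covariance structure would look data-driven.

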### Secondary objectives

1.2

The secondary objective of the study is to examine whether a 12 week celecoxib + TAU is more effective than placebo + TAU in patients aged 18–65 with MDD and IMD characteristics in: reaching treatment response and remission at 12 week follow-up, and improving functioning, lowering fatigue, food craving, and pain at 12 week follow-up.

Additionally, a secondary objective of this study is to better understand how and for whom celecoxib add-on treatment is effective. For this objective, the following biological markers are assessed: CRP, Imterleukine-6 (IL-6), Tumor necrosis factor alpha (TNF-α), cholesterol, triglycerides, glucose, Body Mass Index (BMI), waist and hip circumference. Explorative analyses will be performed on the mediating/moderating role of these markers. These analyses will provide suggestions on whether a potential treatment effect is achieved through modulation of immune-metabolic markers, hypothesized to be at the core of IMD pathophysiology.

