### Study procedure

2.3

To ensure safe participation and to answer the research questions properly, potential participants will undergo an extensive screener procedure. Full in- and exclusion criteria can be found in Table 1.

**Table 1 tbl1:** In- and exclusion criteria for the INFLAMED trial.

Inclusion	Exclusion
➢ Age 18–65 years	➢ Contraindications for celecoxib (history of: peptic ulcers, gastrointestinal bleeding, ischemic heart disease, stroke, heart failure, allergic reactions to aspirin/NSAIDs/coxibs; impaired kidney function (creatinine clearance < 30 ml/min); impaired liver function (ALT > 2x upper limit of normal [ULT]))
➢ DSM-5 diagnosis of MDD confirmed with clinical interview (MINI)	➢ Electroconvulsive therapy (ECT) in the past 3 months
➢ Currently using an SSRI or SNRI; subjects should be on the current medication for at least 4 weeks	➢ Being on antidepressants other than SSRIs or SNRIs or being on other psychotropic drugs
➢ IDS score ≥26 and a score ≥6 on atypical, energy-related symptoms scale from IDS ➢ CRP>1 mg/L	➢ Starting other evidence-based non-pharmacological intervention for depression (e.g. psychotherapy) in the 4 weeks before randomization. Clinically overt alcohol/drug dependence or other primary psychiatric diagnoses (schizophrenia, schizoaffective, Obsessive-compulsive disorder (OCD), or bipolar disorder)
➢ A female participant is eligible to participate if one of the following conditions applies: - She is not a woman of child bearing potential (WOCBP) - She is a WOCBP and is not pregnant or breastfeeding. Furthermore, she agrees to use, or is already using, a contraceptive method during the intervention period and up to 1 month after the intervention. A WOCBP must have a negative highly sensitive pregnancy test before the first dose of the study intervention.	➢ Chronic use of anti-inflammatory drugs and corticosteroids ➢ Current use of anticoagulants
➢ Signed informed consent	➢ Not speaking Dutch

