### Eligibility assessment

2.4

Potential participants will enrol through the study website by filling in the IDS and their age as the first steps of screening, after having read the PIF and online consent for screening.

If participants are eligible for the next step (18–65yr, IDS ≥26, atypical, energy related symptoms ≥6), a video-interview will be planned with a trained researcher. In this interview, participants will have the opportunity to ask questions, before signing informed consent to collect data for further screening. After this, participants undergo the interview for the in- and exclusion criteria mentioned in Table 1, including a diagnostic interview to asses for current DSM-5 diagnosis MDD (American Psychiatric Association, 2013).

If still deemed eligible after the interview and after having returned the signed informed consent to researchers, participants will receive a fingerprick-kit for a blood draw at home (or venepuncture at study site if preferred). If a participant has low-grade inflammation (CRP>1) on this test and if there are no signs of liver problems (ALT ≤ 2x upper limit of normal [ULT]) or kidney problems (creatinine clearance ≥30 ml/min), they can be enrolled in the study. The study flow is displayed in Fig. 1.

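### Response and remission are yes/no, but the plan sends them through the primary's linear mixed model and a baseline-SD effect size that is undefined for both

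*Protocol article*

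**What the plan says.** Section 2.10 (Data analysis) of the protocol article sets out the primary method: "linear mixed models will be used including a random intercept at subject level". In the primary analysis, "fixed effects will consist of treatment, a linear effect of time, and a treatment-by-time interaction". A secondary version dummy-codes time so that group means can be estimated at each visit. Estimates are adjusted for baseline IDS. Standardised effects are the estimated group difference divided "by the SD of the baseline outcome".

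The secondary outcomes are covered by one sentence: "Analysis for the secondary outcomes will follow the same approach as the primary outcomes". The only separate rule is that adverse events are summarised descriptively. The article names no logistic or generalised model, risk difference or odds ratio.

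Section 2.7 (Outcomes) lists the outcomes concerned: "Secondary study outcomes include response (50% reduction in IDS scores), remission (MINI-S diagnostic interview"). Section 1.2 (Secondary objectives) places them in time: "reaching treatment response and remission at 12 week follow-up". They are two of the six efficacy objectives listed there; the others are functioning, fatigue, food craving and pain.

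**The concern.** The rule is written for a continuous score measured repeatedly, including at baseline. Response and remission are not of that kind, in two respects.

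- **Effect size.** Nobody is a responder or a remitter at baseline, so the outcome has no spread there to divide by.
- **Standard error.** A random-intercept linear model, as normally fitted, has one residual variance for all visits. A 0/1 outcome with rate p has variance p(1 − p). That variance is small while few patients have responded and larger later. A pooled value is therefore too small at week 12, the visit the objective names, if response builds up over time.

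Response and remission are the results a clinical reader will look at first after the primary. If the rule is followed literally, one reported quantity cannot be computed and the p-value and interval are unreliable. If it is not followed, the model and effect measure are chosen later, outside the published plan.

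**Working it through.** **1. The plan's own figure.** The only computed design figure is the 83% power in section 2.8. Take total variance 1, ICC 0.5, visits at weeks 2 to 12, a difference growing linearly from 0 at week 0 to 0.52 at week 12, 70 per arm, and dropout rising to 12% and 16%. The treatment-by-time test then has 82.1% power, close to the stated 83%. The point below does not depend on this figure.

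**2. The denominator of the effect size.**

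- Response at baseline: the reduction from a patient's own baseline is (IDS₀ − IDS₀)/IDS₀ = 0, which is below 50%. Response is 0 for all 140.
- Remission at baseline: Table 1 requires "DSM-5 diagnosis of MDD confirmed with clinical interview (MINI"), and section 2.4 describes "a diagnostic interview to asses for current DSM-5 diagnosis MDD". Remission is therefore 0 for all 140, assuming no change in diagnosis between screening and baseline.
- SD of a variable that is 0 for everyone: √[Σ(0 − 0)²/139] = 0.
- Effect size = (difference in proportions)/0, which is undefined. With assumed rates of 30% and 50% (the article gives none), this is 0.20/0.

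Reading the baseline outcome as baseline IDS does not help. A difference in proportions divided by IDS points has no interpretation.

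**3. The standard error at week 12, by hand.** Assume no treatment effect, 70 per arm, and response rising from 1% at week 2 to 30% at week 12. For simplicity take equal steps: 1.0, 6.8, 12.6, 18.4, 24.2 and 30.0%.

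- Variances p(1 − p): 0.0099, 0.0634, 0.1101, 0.1501, 0.1834, 0.2100; mean 0.1212.
- Correct SE of the week-12 difference: √(2 × 0.2100/70) = 0.077.
- SE if the variance is pooled over visits: √(2 × 0.1212/70) = 0.059.
- Two-sided type I error at nominal 5%: 2[1 − Φ(1.96 × 0.059/0.077)], about 14%.

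**4. The same check by simulation.** A simulation under no effect used assumed IDS values giving response of about 1% at week 2 and 30% at week 12.

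| Quantity | Result |
|---|---|
| Model SE, week-12 difference | about 0.054 |
| Empirical SE | about 0.076 |
| Type I error, week-12 difference | about 16% |
| Type I error, slope test | about 10% |

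These agree with each other: 2[1 − Φ(1.96 × 0.054/0.076)] = 16%. The empirical SE is also close to the hand value of 0.077.

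A second simulation used different assumptions (baseline IDS mean 40, SD 9; no dropout; 400 runs). It gave a model SE of about 0.057 against 0.071 and a type I error near 13%. With 400 runs, the simulation error on that figure is about √(0.13 × 0.87/400) = 1.7 percentage points.

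**5. The point estimate.** In the second set of assumptions with a treatment effect, the dummy-time model's week-12 estimate averaged 0.181, equal to the raw risk difference of 0.181. The estimate is usable; the standard error is not.

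**The case against.** The strongest reply is that the article condenses a full protocol. On this view, same approach means intention-to-treat, mixed models over all follow-ups and adjustment for baseline IDS, with the link function for binary outcomes left to an analysis plan. That reading is possible, but the text names only linear models and makes one exception, for adverse events. The baseline-SD effect size fails even under a generalised mixed model. This is a stated rule that does not fit, not a missing detail.

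It can also be said that a division by zero is noticed at once and misleads nobody, and that it touches only a supplementary measure. That stands for the effect size. It does not answer the standard-error problem, which would not be noticed.

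A reader might infer three stronger claims that the article does not support:

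- **That the covariate is a constant.** The plan adjusts for baseline IDS, which varies between patients. The claim would hold only for adjustment on each outcome's own baseline value.
- **That there is one value per patient, so the random intercept cannot be estimated.** Response can be derived from the IDS at all six follow-ups. Interviews take place at weeks 2, 6 and 12, and whether the MINI-S is given at each is in Table 2, which is not shown. Setting the objective at week 12 does not imply a single measurement, since the same objective covers functioning, fatigue, food craving and pain.
- **That no valid estimate exists.** The dummy-time model gives a usable week-12 risk difference for response.

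**Conclusion.** The rule is wrong as written for response and remission. The standardised effect size is undefined for both. This follows from the definition of response and the entry criterion for MDD, apart from the small assumption that diagnosis does not change between screening and baseline.

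For response, the linear model's standard error at week 12 is too small when the rate rises over follow-up. Type I error was about 13% to 16% in the simulations, against a nominal 5%. That size rests on assumed IDS values, on rates rising from near zero, and on a constant residual variance, the usual default. With other rates it would differ. For remission the size cannot be given, because the visits with a MINI-S are not shown.

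Severity is moderate. Two secondary outcomes are affected; the primary analysis and the sample size are not.

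**What to change.** - Limit the sentence on secondary outcomes, and the effect size divided by the baseline SD, to continuous outcomes measured repeatedly.
- State that response and remission at week 12 are analysed with a binary-outcome model adjusted for baseline IDS. This can be logistic regression, or a logistic mixed model over the available visits, which stays closer to the present approach.
- Report a risk difference or odds ratio with 95% CI.
- Say how patients without a week-12 value are handled. The planned dropout of 12% and 16% is 70 × 0.12 + 70 × 0.16 = 8.4 + 11.2, about 20 of 140 patients. The maximum-likelihood argument in section 2.10 is made for the linear mixed model and does not carry over to a week-12-only logistic regression. Whether to impute, and how, is for the sponsor to choose.

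The cost is a few sentences and routine code. No new data are needed, and it can be done before database lock.
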